# POPPIE: protocol for a randomised controlled pilot trial of continuity of midwifery care for women at increased risk of preterm birth

**DOI:** 10.1186/s13063-019-3352-1

**Published:** 2019-05-14

**Keywords:** Preterm birth, Maternity care, Maternal health services, Models of care, Continuity of care, Hybrid type 2 implementation/effectiveness trial, MRC guidance complex interventions

## Abstract

**Background:**

High rates of preterm births remain a UK public health concern. Preterm birth is a major determinant of adverse infant and longer-term outcomes, including survival, quality of life, psychosocial effects on the family and health care costs. We aim to test whether a model of care combining continuity of midwife care with rapid referral to a specialist obstetric clinic throughout pregnancy, intrapartum and the postpartum period is feasible and improves experience and outcomes for women at increased risk of preterm birth.

**Methods:**

This pilot, hybrid, type 2 randomised controlled implementation trial will recruit 350 pregnant women at increased risk of preterm birth to a midwifery continuity of care intervention or standard care. The intervention will be provided from recruitment (antenatal), labour, birth and the postnatal period, in hospital and community settings and in collaboration with specialist obstetric clinic care, when required. Standard care will be the current maternity care provision by NHS midwives and obstetricians at the study site. Participants will be followed up until 6–8 weeks postpartum. The composite primary outcome is the appropriate initiation of any specified interventions related to the prevention and/or management of preterm labour and birth. Secondary outcomes are related to: recruitment and attrition rates; implementation; acceptability to women, health care professionals and stakeholders; health in pregnancy and other complications; intrapartum outcomes; maternal and neonatal postnatal outcomes; psycho-social health; quality of care; women’s experiences and health economic analysis. The trial has 80% power to detect a 15% increase in the rate of appropriate interventions (40 to 55%). The analysis will be by ‘intention to treat’ analysis.

**Discussion:**

Little is known about the underlying reasons why and how models of midwifery continuity of care are associated with fewer preterm births, better maternal and infant outcomes and more positive experiences; nor how these models of care can be implemented successfully in the health services. This will be the first study to provide direct evidence regarding the effectiveness, implementation and evaluation of a midwifery continuity of care model and rapid access to specialist obstetric services for women at increased risk of preterm birth.

**Trial registration:**

ISRCTN37733900. Retrospectively registered on 21 August 2017.

## Background

Preterm birth (PTB) is a birth that occurs at < 37 weeks of gestation. PTB rates are increasing worldwide, despite advances in antenatal care [1]. The cost of PTB to the UK National Health Service (NHS) is estimated to exceed £3 billion per annum [2]. PTB is associated with poorer quality of life [3], with no single strategy effective in reducing rates [4]. There are multiple known risk factors associated with early birth including previous PTB, late miscarriage and cervical surgery, but the cause of spontaneous PTB is unknown in approximately 40–50% of cases [5].

A Cochrane review of 15 trials involving 17,674 women reported that women randomised to receive continuity of care by one named midwife, or a small group of midwives, during pregnancy, birth and the postnatal period were significantly more likely to be attended at birth by a known midwife. They were significantly less likely to experience PTB or fetal loss/neonatal death before 24 weeks and had fewer fetal/neonatal deaths in total [6]. There is also evidence of increased referral to specialist services and clinical benefit for women with social complexity [7].

Screening and managing women at increased risk of PTB in specialist obstetric clinics is now considered useful [8]. However, PTB clinics or preterm surveillance clinics are rarely available outside research settings, and women who require specialist medical and obstetric expertise often receive fragmented midwifery care. Continuity of carer is identified in the current maternity policy document ‘Better Births’ as a model of care that the NHS England is committed to increase. However, around 75% of women have not met the midwife who attends their birth beforehand [9]. Our research [10–12] provides a basis to develop and test the impact of a novel care pathway for women at increased risk of PTB, which combines continuity of midwife care with rapid referral to a specialist obstetric clinic throughout pregnancy through to the intrapartum and postpartum periods [13].

POPPIE (Pilot study Of midwifery Practice in Preterm birth Including women’s Experiences) is a pilot, hybrid, type 2 randomised controlled implementation trial to determine whether this model of continuity of care is feasible, and could improve pregnancy outcomes and women’s experiences. The setting will be an inner-city hospital in South London.

The TIDieR guidance [14] will be used to describe the intervention and standard care. In order to clarify assumptions in relation to how the intervention will be implemented, and the mechanisms through which it will produce change in this context, a logic model informs data items for the implementation outcomes assessment [15] (Fig. 1). We will use the Reach Effectiveness Adoption Implementation Maintenance (RE-AIM) [16] and Medical Research Council (MRC) [17] guidance for the evaluation of complex interventions to assess feasibility, acceptability to staff and women, adoption, fidelity, reach, equity, penetration, costs and sustainability, and to inform implementation and the mechanisms of impact on maternal and neonatal health, women’s experiences of care and quality of care.

**Fig. 1 Fig1:**
[figure not shown]
POPPIE logic model for research

### How the intervention may work?

Continuity of care is defined as delivering care that acknowledges that a woman’s health needs are related to events and should be managed over time [6]. Therefore, midwifery continuity of care allows women to develop a relationship with the same caregivers throughout pregnancy, birth and the postnatal period. Women have a named and a ‘backup’ midwife, from the same team, caring for them during labour, birth and the postpartum period, whom they have met before and feel they know. This trusting relationship may increase their confidence and reduce levels of psychosocial stress [18, 19]. This close relationship between women and midwives may also help women feel that they have a health care provider who knows their medical history who will be caring for them throughout labour, birth and the postnatal period [20, 21]. The trust and feeling of safety that this may afford may mean that women are more willing to accept help from psychiatric services, domestic violence advocacy and other services, where required. Women may be more likely to talk about lifestyle choices, such as smoking and drinking, and to trust the advice they receive [7, 22]. However, women may also be unhappy with a perceived intrusive surveillance.

It is also hypothesised that there is an improved co-ordination and collaboration between midwives working in continuity models of care and the multi-disciplinary network of support, improved access to care, improved care according to guidelines, earlier recognition of problems and improved health behaviours. Thus, the initiation of treatments to prevent or reduce PTB may occur earlier in the intervention group because the midwives have greater knowledge, there are lower barriers for women to contact midwives and faster access to obstetric opinion and management.

## Methods

The aim of this study is to test in a pilot study if a model of care combining continuity of midwife care with rapid referral to a specialist obstetric clinic for women at increased risk of PTB is feasible and improves experience, pregnancy outcomes and quality of care. If feasibility is confirmed, learning from this pilot trial will inform a full-scale multi-centre trial, following the MRC guidelines [17] – aimed at improving outcomes and reducing the incidence and appropriate and timely management of PTB.

### Design, setting and population

We will undertake a two-armed, parallel-design, individually pilot randomised controlled trial. A type 2 hybrid design will place equal focus on evaluating the effectiveness of the intervention and the implementation [23]. The study will be undertaken in an inner-city hospital in South London with a higher than national average PTB rate (8.2 vs 7.2% in England) [24]. The study population will include pregnant women booking for antenatal care, identified as at increased risk of PTB and residing in the hospital catchment area in the study period (Fig. 2).

**Fig. 2 Fig2:**
[figure not shown]
Standard Protocol Items: Recommendations for Interventional Trials (SPIRIT) adapted for the POPPIE trial

### Participants

We will include asymptomatic pregnant women with singleton pregnancies attending for antenatal care at less than 24 weeks’ gestation and identified at increased risk of PTB – fulfilling one or more of the following criteria: previous cervical surgery (such as cone biopsy, loop diathermy); uterine abnormality (such as bicornuate uterus); previous short cervix or short cervix this pregnancy (< 25 mm); previous cerclage; previous premature ruptured membranes (< 37 weeks); one or more previous PTB (< 37 weeks); one or more previous late miscarriage/abortion (> 14 weeks); current smoker of tobacco, as identified at first antenatal appointment. We will exclude women aged < 18 years at recruitment, multiple pregnancies, unable/unwilling to give informed consent and those already receiving care from a specialist midwifery team (e.g. women with severe mental illness, diabetes, alcohol and substance misuse).

### Identification, screening, recruitment and randomisation

Trial information will be available in all relevant clinical areas including maternity services, general practice surgeries and health centres. Community midwives and other maternity care clinicians will refer women who express an interest in the study to the midwifery team leader to discuss trial participation. At early nuchal and/or anomaly ultrasound scan appointments, women who meet inclusion criteria will be offered verbal and written information about the study. Potentially eligible women will also be identified by review of medical records and appointment lists by clinical staff. In these cases, women will be contacted by a member of the direct clinical team to discuss their eligibility and study participation and sent a leaflet by post/email to read (if interested) before their appointment attendance. Adequate time will be given to interested women to explain the study, for considering participation, and asking any questions with members of the clinical team. All participants will provide written informed consent prior to participation.

Baseline data will be collected, and participants randomised in a 1:1 ratio to receive either POPPIE care or routine standard care. Randomisation will be managed via a secure web-based randomisation system (MedSciNet™), which is part of a password-protected Internet-based study specific data management system. A minimisation algorithm will be used to ensure balance between the groups with respect to smoking at booking and previous PTB (< 37 weeks). The nature of the intervention is such that blinding of participants and care providers cannot be achieved. However, risk of bias will be reduced since data will be processed by researchers blinded to the model of care that the women is allocated to. The flow diagram of participants though the study is shown in Fig. 3.

**Fig. 3 Fig3:**
[figure not shown]
Flow diagram of participants

### Intervention: POPPIE midwifery team

Women allocated to the intervention group will receive a continuity of midwife care model during the antenatal, labour, birth and postnatal periods, predominantly from one midwife and her partner midwife (backed up by the rest of the POPPIE team). Midwives will ‘follow women’ and scheduled and out of hours’ antenatal, intrapartum and postnatal care may be provided in hospital, community/children’s centres or at home. Midwives will provide continuity of care in a multi-disciplinary network of consultation and referral with other care providers. Some antenatal and/or intrapartum and/or postpartum care will be provided in consultation with medical staff, as appropriate [5]. Within this model, midwives work in partnership with the woman; they are the primary professional with responsibility for assessment of needs, planning care, referral to other professionals as appropriate, and for ensuring co-ordination of services. Clinical care content will follow NHS Trust hospital guidelines. The team will have rapid access using a mobile phone to a linked consultant obstetrician with specialist expertise in PTB to refer and/or discuss any clinical concerns, issues or queries.

The POPPIE team will include six Whole-time Equivalent (WTE) midwives, including an experienced senior midwife who leads the team. Specialist training (preventing and managing PTB; caring for preterm infants; bereavement; working in midwifery continuity of care models), research training (Good Clinical Practice); valid informed consent; data collection and data entry) and ongoing support will be provided following a training needs assessment.

### Control: Standard midwifery care

Women allocated to standard care will receive care as appropriate from the local maternity services in line with usual practice at the study site, across the antenatal, labour, birth and postnatal periods. Antenatal care is provided by different midwives working in the community, children’s centres, and/or hospital. Some antenatal and/or intrapartum and/or postpartum care is also provided in consultation with medical staff as appropriate. Core hospital midwives and/or physicians in the birth centres and/or labour ward provide labour and birth care and midwives in the postnatal ward provide postnatal care. Women are also offered midwifery visits at home and in postnatal clinics in the community following discharge from hospital by a range of midwives. Clinical care content follows Trust hospital guidelines. Midwives in the standard care arm do not have a linked obstetrician working directly with them and they may have to contact on-call obstetric registrars, obstetricians or other services (e.g. antenatal clinics, day assessment unit) to discuss any clinical concerns, issues or queries or make referrals.

### Intervention and control: Obstetric care pathway

In accordance with the hospital guidelines, women identified as being at increased risk of PTB in both trial arms are seen by a consultant obstetrician as soon as possible after their nuchal scan to discuss an individual care plan based on their obstetric and medical history. Women in both trial arms with specific risk factors for PTB are then followed up weekly or 2-weekly from 14 to 24 weeks’ gestation in the cervical scan clinic, as considered necessary. Depending on risk factors, women may be referred to a consultant obstetrician and/or offered additional tests (e.g. a transvaginal scan, a urine test and/or a vaginal swab, a fetal fibronectin test) and other preterm interventions according to Trust guidelines (e.g. cervical cerclage, antibiotics, progesterone, steroids) with follow-up appointments in the clinic up to 30 weeks of pregnancy.

### Outcomes and measures

#### Primary outcomes

The composite primary outcome is the initiation of any of the following interventions appropriately provided for the prevention and/or management of preterm labour and birth (antibiotics for urinary tract infections, smoking cessation and domestic violence advocacy referrals, transvaginal scan assessments of the cervix, fetal fibronectin assessments, cerclage insertion, progesterone administration, corticosteroid administration, magnesium sulphate administration, admission for observation and in utero transfer). A composite outcome is chosen, as the primary outcome as powering a pilot trial for PTB alone would require too large a sample size, and helps the investigators to avoid an arbitrary choice between several important outcomes that refer to the same disease process [25]. We will report the effect of the continuity of care model on both the composite and its components for all woman in the study, specifying if (1) an intervention was required and (2) the intervention was provided. Women who experience any one of the intervention components will be considered to have experienced the composite outcome.

#### Secondary outcomes

The secondary outcomes are related to recruitment and attrition rates; acceptability to women, health care professionals and stakeholders; health in pregnancy and other complications; labour and birth outcomes; maternal and neonatal postnatal outcomes; assessment of psycho-social health; quality of care and women’s experiences of trust, stress, system responsiveness and safety. Measures of implementation outcomes (acceptability, adoption, reach, fidelity, appropriateness, penetration, costs, resource use and sustainability) will be guided by the RE-AIM Framework [16].

### Data collection

Demography, medical history and current pregnancy health information and psycho-social health data will be collected prior to randomisation at baseline visit (recruitment). Follow-up data will continue up to 6–8 weeks postpartum for mothers and until discharge from neonatal intensive care unit (NICU) for babies (up to 3 months). Pregnancy outcome, birth and neonatal data will be collected from maternal and infant medical records and NHS electronic data systems. Data from validated questionnaires at baseline and postnatally (e.g. Prenatal Distress Questionnaire [26], Everyday Discrimination Scale [27], PHQ1 Mental Health [28], PROMIS-10 Health Related Quality of Life [28], Labour Agentry Scale [29], Mother-to-Infant Bonding Scale [28, 30], Trust in Nurses Scale [31], Social Support [32]) will be used to assess health and wellbeing, and measure women’s experiences, continuity, quality of care and safety. Data will be anonymised and entered onto the secure, password-protected MedSciNet™.

### Withdrawal

Participants can withdraw at any point without giving a reason. Women may be withdrawn from the trial if midwifery specialist care is required (e.g. mental health support). Permission will be sought to access routinely collected clinical pregnancy outcome data.

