#### Proposed statistical analysis

The analysis will be ‘intention to treat’, including withdrawals and losses to follow-up. Randomisation should ensure that the groups are similar or equivalent in their baseline characteristics; additional multivariate analysis will be used if baseline differences are noted between the two groups.

The relative risks (with 95% confidence intervals) of the component primary outcomes will be calculated. Secondary outcome measures of categorical data will be analysed with *χ*^2^ tests and continuous data will be analysed with *t* tests (for normally distributed data). Ranked or Likert-scale data will be analysed using cumulative odds ratios. Logistic regression and multiple linear regressions will be used if necessary to adjust for any other confounding variables. Outcome assessments and analysis will be blinded.

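### The withdrawal rule does not separate a move to specialist midwifery care from the end of follow-up, so psychosocial and experience outcomes may be lost selectively by arm

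*Protocol article*

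**What the plan says.** The Withdrawal section of the protocol article has three elements. A woman may leave at any time without giving a reason. Separately: "Women may be withdrawn from the trial if midwifery specialist care is required (e.g. mental health support"). Then: "Permission will be sought to access routinely collected clinical pregnancy outcome data".

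Other sections bear on this rule:

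- **Proposed statistical analysis** calls the analysis intention to treat, "including withdrawals and losses to follow-up".
- **Participants** excludes, before randomisation, "those already receiving care from a specialist midwifery team (e.g. women with severe mental illness, diabetes, alcohol and substance misuse"). The withdrawal rule is the counterpart of this exclusion during the trial.
- **How the intervention may work?** suggests that trust in a known midwife may mean that "women are more willing to accept help from psychiatric services, domestic violence advocacy and other services, where required".
- **Background** adds: "There is also evidence of increased referral to specialist services and clinical benefit for women with social complexity".
- **Data collection** states: "Pregnancy outcome, birth and neonatal data will be collected from maternal and infant medical records and NHS electronic data systems". Mental health, quality of life, labour agentry, bonding, trust and social support come from questionnaires at baseline and postnatally.
- **Identification, screening, recruitment and randomisation** accepts that participants and care providers cannot be blinded.

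**The concern.** A woman who needs a specialist midwifery team has had a change of care. That alone is no reason to stop observing her, yet the rule speaks of leaving the trial, and the decision is not hers.

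The trigger may not be neutral between arms. The protocol's own account of the mechanism has continuity of care increasing the uptake of specialist help. If that happens, part of the hypothesised benefit could also end a woman's participation, and could do so more often in one arm.

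The outcomes most exposed are those that records cannot supply. Improved experience is part of the stated aim (Methods), and psychosocial health and women's experiences are named secondary outcomes. Women withdrawn for mental health need are likely to be among those with the worst scores. If more of them leave the intervention arm, the women remaining there would look better than the arm as randomised.

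**Working it through.** **1. The plan's own figure.** Inputs from Sample size calculation: 40% v 55%, 175 per arm. Two-sided alpha of 0.05 is assumed, in line with the 95% confidence intervals. With the pooled proportion p̄ = 0.475:

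n = [1.96·√(2·0.475·0.525) + 0.842·√(0.40·0.60 + 0.55·0.45)]² / 0.15² = 172.8, so 173 per arm.

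Power at 175 per arm is 80.5%. The stated 80% is reproduced. The figure of 350 is both the recruitment target and the number in the power statement, and no allowance for loss is stated.

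**2. What remains observable after a withdrawal under this rule.**

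| Outcome type | Source | Provision after withdrawal |
|---|---|---|
| Pregnancy, birth, neonatal | Medical records, NHS systems | Yes, if permission is given; timing of the request not stated |
| Psychosocial, trust, bonding, experience | Postnatal questionnaires | None stated |

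**3. Primary outcome.** If records are obtained for every withdrawn woman and she is analysed as randomised, nobody is missing and the bias is zero.

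If records were not obtained, let a fraction w of an arm be lost, and let r be the composite rate among those lost. The observed rate is (p − w·r)/(1 − w). Every w and r below is an assumption, because the document gives none.

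Loss from the intervention arm only, true rate 55%:

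| w | r = 80% | r = 20% |
|---|---|---|
| 5% | (0.55 − 0.04)/0.95 = 53.7% | (0.55 − 0.01)/0.95 = 56.8% |
| 10% | (0.55 − 0.08)/0.90 = 52.2% | (0.55 − 0.02)/0.90 = 58.9% |

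The shift runs from about −3 to +4 points, against a target of 15.

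Loss from both arms, true difference 15 points:

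| Lost, intervention v control | r | Observed, control v intervention | Difference | Power |
|---|---|---|---|---|
| 10% v 3% | 90% | 38.5 v 51.1% | +12.7 | 63% |
| 10% v 3% | 20% | 40.6 v 58.9% | +18.3 | 91% |
| 5% v 2% | 90% | 39.0 v 53.2% | +14.2 | 75% |
| 5% v 2% | 20% | 40.4 v 56.8% | +16.4 | 86% |

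The direction is set entirely by r.

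**4. Loss of numbers alone, without bias.** Power falls to 78.5% with 5% lost in both arms and to 76.2% with 10%. This is minor beside the selection problem.

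**5. Questionnaire outcomes.** Suppose withdrawn women would have scored d worse on average than those who stay, with the same d in both arms. Losing a fraction w makes an arm look better by w·d, so the between-arm bias is d·(w_intervention − w_control). At the assumed rates this is 0.10d − 0.03d = 0.07d, or 0.05d − 0.02d = 0.03d. It favours the intervention if withdrawal is more frequent there, and is zero if withdrawal is equal across arms. The document supplies neither d nor w.

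**The case against.** A reader might infer that the rule removes women from the analysis and so contradicts intention to treat. The document does not support that. The analysis section expressly counts withdrawals in, the Withdrawal section plans access to routine records, and no sentence excludes withdrawn women. This part of the objection stands in full.

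A reader might also infer that the trigger must fire more often in the intervention arm. The text is weaker. It says women may be more willing to accept psychiatric and other services, whereas the trigger is that specialist midwifery care is required. These are not the same event. Together with the cited evidence on referral, a difference between arms is plausible, but it is not established.

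Nor is the trigger itself a component of the primary outcome. The referrals listed are "smoking cessation and domestic violence advocacy referrals"; mental health referral and transfer to a specialist midwifery team do not appear. The power figures in the working assume that withdrawn women's records are lost, which is not what the plan intends.

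Two further points are fair. The permission could be part of the consent taken at entry, and the consent form is not shown. Also, no sentence says that questionnaires cease; this is only the natural reading of leaving the trial when the sole provision made afterwards is for routine clinical data. Attrition is to be reported, and the handling of missing data may sit in an analysis plan not shown here.

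Finally, Trial status gives the end of recruitment as 30 September 2018, before the article appeared in May 2019, so new wording could protect few women in this trial.

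What survives is the rule as stated. It ends trial participation for a reason that calls only for a change of provider, and its one safeguard does not reach the questionnaire outcomes. Better handling of missing data would not recover data that need not have been lost.

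**Conclusion.** The point holds as a weakness in a stated rule. It undermines the intention-to-treat analysis without contradicting it. The main exposure is selective loss in the psychosocial and experience secondary outcomes, where routine records are no substitute.

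For the primary outcome the bias is zero if records are obtained. If they are not, it could go either way: about −3 to +4 points for a one-arm loss of 5 to 10%, under assumed event rates of 80% and 20% among those lost. For questionnaire scores the bias equals the difference in withdrawal rates multiplied by the score gap between women who leave and women who stay.

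The actual size cannot be computed, because the document gives no withdrawal rate. The conclusion rests on two readings: that leaving the trial includes leaving questionnaire follow-up, and that withdrawal could plausibly differ by arm when care providers are unblinded.

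**What to change.** Reword the rule to say that a woman whose care moves to a specialist team remains in the trial and in her allocated arm, with records and questionnaire follow-up continuing unless she herself withdraws. The decision about her care is untouched; only her trial status is clarified. Say also when the permission for routine data is obtained.

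Since recruitment has closed, the practical form for this trial is mainly the following:

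- Obtain routine outcome data through the permission route for every woman withdrawn under the rule.
- Report the number so withdrawn, by arm and reason.
- Analyse these women as randomised.
- Add a sensitivity analysis for missing questionnaire outcomes that lets women withdrawn for specialist care have worse scores than those observed.

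The full-scale trial that this pilot is meant to inform should carry the revised wording from the start.

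The cost is a change of wording, possibly a matching line in the consent form, and a modest amount of retrieval and analysis using records and questionnaires already planned. The downside is that some women in the intervention arm receive less of the intervention, a slight dilution that intention to treat accepts.
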